### Interventions

All stroke survivor participants (irrespective of randomisation allocation) will receive usual care within an organised stroke service. In line with the pragmatic nature of the trial, the comparator is ‘usual care’ as determined by local policy and practices, to draw comparison with current practice in NHS stroke services, especially given the variation in pathways. Information on the care delivered by both control and intervention sites will be captured by survey and enhanced by conversations with clinical staff (if further details are required) prior to randomisation and at regular intervals (approximately every 3−6 months) until the end of the trial. Observations conducted as part of the embedded process evaluation will provide additional insights into the nature of usual care provision at both control and intervention sites. This information will also provide context for trial implementation and monitor any potential contamination and/or confounding between the two arms of the trial.

In stroke services allocated to the intervention arm, participants will also receive the Get Set Go intervention. Get Set Go is a whole-service intervention designed to be implemented and embedded within routine practice. Delivery commences in the inpatient stroke unit setting and continues into the community for at least 12 weeks post-discharge. The intervention focuses on:

Educating staff and stroke survivors (and their family/friends/carers where appropriate) about the importance of standing and moving after stroke.Preparing and enabling staff to support and encourage stroke survivors to stand and move more in everyday stroke care (as part of routine practice).Encouraging stroke survivors to monitor their own standing and moving, with assistance from family/friends/carers where appropriate.

As Get Set Go will be delivered at service level, all clinical staff members working within the stroke services randomised to deliver the intervention (ie, inpatient and community settings) will be invited to attend a training session (~1 hour) to prepare for delivering Get Set Go. This will include the intervention rationale and an overview of key components. Staff will participate in practical tasks to ensure they feel confident in supporting and encouraging stroke survivors, who are capable of standing independently/with the assistance of one person, to stand and move more in everyday stroke care (ie, as part of routine clinical practice). A Template for Intervention Description and Replication checklist^24^ will be published with trial findings. There are no special criteria for discontinuing or modifying allocated interventions. Recommendations for standing and moving are made by staff as part of delivering the intervention alongside usual care in the stroke unit or community setting, based on their usual assessment techniques and clinical judgement. These recommendations will be regularly reviewed and modified in line with stroke survivors’ individual capabilities and circumstances.

There are no provisions in place for post-trial care beyond the standard care provided within the participating NHS stroke services.

### Study Within A Trial

This cRCT will also incorporate a Study Within A Trial (SWAT) (protocol reported separately),^25^ to evaluate whether a video animation could increase participant understanding of the intervention, and result in improved engagement and compliance, potentially resulting in improved outcomes. Intervention sites will be randomised 1:1 to the SWAT intervention (Get Set Go plus video animation) or control (Get Set Go with no video animation). Results will be reported separately.

### Strategies to improve intervention adherence

The implementation team will maintain regular contact with clinical leads in sites allocated to the intervention arm to monitor delivery of the intervention and provide support as required. Clinical staff who are responsible for delivering the intervention will also complete monitoring records for all stroke survivors (whether or not they are trial participants) to document whether key tasks relating to the intervention have been completed (no personal data will be recorded for non-trial participants). It will be advised that a nominated member of staff checks these records have been completed on a regular basis (eg, towards the end of each shift). Regular review of these records will enable the study team to monitor intervention adherence and provide insight into intervention delivery. A short postal questionnaire completed by stroke survivor trial participants at 12 weeks post-hospital discharge will also assess intervention compliance, with those in the intervention arm responding to questions about the intervention; all participants will be asked about falls and use of a walking aid. Data on compliance will be analysed using descriptive summary statistics by allocation. Finally, intervention fidelity will be explored separately within the process evaluation, through site-based observations of intervention delivery, interviews with those delivering and receiving the intervention and documentary analysis (including completed intervention materials).

### Endpoints

The primary endpoint is stroke survivor self-reported EADLs at 12 months post-registration. The key secondary endpoint is mean daily sedentary time (minutes) at 12 months post-registration using activity monitor (activPAL) data, which provides a valid measure of posture and transitions in people with impaired mobility.^26^ Other secondary endpoints at 6, 12 and 24 months post-registration (unless stated otherwise) for stroke survivor participants are listed below:

Sedentary behaviour measured by activity monitor.EADLs (at 6 and 24 months only) measured by Nottingham Extended Activities of Daily Living scale (NEADL).^27^
Health and disability measured by WHO Disability Assessment Schedule 2.0 (12-item).^28–32^
Mental well-being measured by Warwick-Edinburgh Mental Well-being Scale.^33^
Health status measured by European Quality of Life 5-Dimension Health Questionnaire (5 levels; EQ-5D-5L).^34^
Quality-adjusted life year (QALY) gains (as above).Fatigue as measured by Fatigue Assessment Scale.^35 36^
Death.Falls and use of a walking aid (12 weeks post-discharge, and at 6, 12 and 24 months).Self-reported sedentary behaviour measured by the Measure of Older Adults’ Sedentary Time^37^ and a Sedentary Behaviour Visual Analogue Scale (adapted from Chastin *et al*, 2019^38^).Institutionalisation, hospital readmission and emergency department attendance rates.Cardiovascular risk markers: Body mass index (BMI), waist circumference, blood pressure (BP).Total major vascular events: Composite measure of non-fatal stroke, non-fatal myocardial infarction or death due to any vascular cause (including unexplained sudden death).^39^
Self-reported health and social care service use and informal care inputs measured by a Client Services Receipt Inventory (CSRI) specifically adapted for this trial from versions used in previous stroke rehabilitation trials.^40 41^
Costs from a health and social care perspective, and a societal perspective that further includes informal care.

The carer endpoint is caregiver burden measured by Modified Caregiver Strain Index^42^ at 6, 12 and 24 months.

An overview of which assessments are undertaken at each time point and the method of completion is provided in table 3. Information about the validity and reliability of the measures used is available in online supplemental appendix 1. Stroke survivors will also complete an additional brief postal questionnaire at 12 weeks post-discharge.

10.1136/bmjopen-2023-074607.supp1Supplementary data

**Table 3 T3:** Overview of assessments and method of completion at each study time point

Outcome/assessment	Method of completion	Time point			
		Baseline	6 months post-registration	12 months post-registration	24 months post-registration
Stroke survivor					
Demographic details	Self-report	X			
Nottingham Extended Activities of Daily Living Scale^27^	Self-report	X	X	X	X
WHO Disability Assessment Scale 2.0 12-item^28–32^	Self-report	X	X	X	X
Warwick-Edinburgh Mental Well-being Scale^33^	Self-report	X	X	X	X
European Quality of Life 5-Dimension Health Questionnaire^34^	Self-report	X	X	X	X
Fatigue Assessment Scale^35 36^	Self-report	X	X	X	X
Measure of Older Adults’ Sedentary Time^37^	Self-report	X	X	X	X
Sedentary Behaviour Visual Analogue Scale (adapted from 38)	Self-report	X	X	X	X
Use of a walking aid	Self-report	X	X	X	X
Falls question	Self-report	X	X	X	X
Hospital admissions	Self-report/electronic health records		X	X	X
Client Service Receipt Inventories to collect data on health and social care use and informal care inputs (adapted from 40 41)	Self-report	X	X	X	X
Total major vascular events^39^	Electronic health records via routine data providers	X	X	X	X
Sedentary behaviour—activPAL measurements	Researcher administration/post	X	X	X	X
Risk markers for cardiovascular disease (height* and weight for body mass index; waist circumference; blood pressure) *Collected at baseline only	Researcher collection from notes/researcher visit/self-completion	X	X	X	X
Adverse events	Self-report/electronic health records		X	X	X
Survival status	Researcher collection from electronic health records		X	X	X
Admission to institution	Self-report		X	X	X
Carer					
Demographic details	Self-report	X	(X)	(X)	(X)
Modified Caregiver Strain Index^42^	Self-report		X	X	X
Employment/occupation status	Self-report	X	X	X	X

(X) only collected if ‘new carer’.

### Randomisation and blinding

Site randomisation will be performed centrally by the Clinical Trials Research Unit (CTRU) and the allocation sequence will be computer-generated using a minimisation programme incorporating a random element to ensure the treatment arms are well-balanced. Eligible stroke services will be randomised on a 1:1 basis either to intervention or control, stratified by:

Sentinel Stroke National Audit Programme (SSNAP) grading level:^43^ A versus B/C/D/E (based on the latest available audit data at the time of randomisation: A=first class service, B=good/excellent in many aspects, C=reasonable overall, some areas require improvement, D=several areas require improvement and E=substantial improvement required).Stroke service composition: Single or combination of trusts.Stroke unit size (acute): Median cut-off of ≤24 and >24 beds based on SSNAP acute organisational audit data (type 2 (solely for patients >72 hours post-stroke) and type 3 beds (used for both pre-72-hour and post-72-hour care) combined—based on the SSNAP audit data and confirmation by site).

Concealment of sequencing is ensured by the physically separate locations of the CTRU (where the randomisation outcome is stored) and the blinded study researchers. Following the randomisation, unblinded members of the study team, the principal investigator at the site and clinical staff who will be involved in intervention delivery, will be informed of the randomisation outcome via secure email to facilitate organisation of intervention training in services allocated to this arm. Local researchers responsible for participant recruitment will be notified that randomisation has taken place but will remain blinded to randomisation outcome and will operate independently of the clinical staff involved in intervention delivery.

Local researchers involved in participant recruitment and in-person data collection (including at baseline, administering activity monitors and assessment of cardiovascular risk markers) will be blinded to the treatment allocation for their site. At the follow-up time points, participant-completed outcome measures will be administered by CTRU staff via postal questionnaire, eliminating the potential for interviewer bias. The activity monitor (on which data is recorded and stored until download) is sealed with no external indication of recording therefore it is not open to bias. Finally, data on mortality, readmissions and use of institutional care will be collected from independent sources and are unlikely to be subject to bias. Instances of unblinding will be recorded via staff self-report.

Participants, clinical staff involved in intervention delivery and the statistical team analysing the outcome data, will not be blinded to treatment allocation. However, to minimise treatment bias, clinical staff involved in intervention delivery will not be overtly informed of which patients are participating in the trial. Additionally, to monitor for potential selection bias, key characteristics of included trial participants will be compared with publicly available data sets (eg, SSNAP^43^) to monitor for evidence of selection bias.

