The local researcher will administer baseline questionnaires to stroke survivor and carer participants face-to-face and offer support where required. Proxy completion of questionnaires by a carer, family member or friend will be permitted (for those with and without capacity), with separate proxy questionnaires provided if required. Stroke survivors will also be asked to continuously wear an activPAL activity monitor on the thigh of their strongest/unaffected leg for 9 consecutive days. The monitor will be attached by the local researcher. They will also be asked to complete a purposely developed daily diary. This will capture if/when the monitor has been removed; the time they went to bed and got up each day and whether they had episodes of sleep (ie, naps) during the day. This information will assist with analysis and facilitate monitoring of adverse reactions to the materials used to attach the monitor. Local researchers will also collect data on risk markers for cardiovascular disease through face-to-face assessment or retrieval from medical records. These include height and weight (for calculation of BMI), waist circumference and BP.

At the follow-up time points (6, 12 and 24 months post-registration), participant-completed outcome assessments will be administered by post in an assessment pack, including a covering letter and a prepaid envelope for postal return. Activity monitors may be administered face-to-face by a local researcher or alternatively, be sent by post to the participant and returned via prepaid envelope. Cardiovascular risk markers (with the exception of height) will be collected alongside the activity monitor assessment. If it is not possible to organise a face-to-face visit, with the participants’ agreement, options for self-assessment will be explored. Guidance will be provided to local researchers as to the action required if a BP reading is abnormal, including reporting this to a named clinician or notifying the participant’s general practitioner (GP). The participant will also be encouraged to discuss this with their GP.

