### Data management

Data will be monitored for quality and completeness using established verification, validation and checking processes, for example, double data entry, and securely stored. Received activPAL data will be subject to quality checks by researchers and where needed, additional details to aid interpretation will be sought from the recruiting site and/or participant diaries. All data collected during the course of the trial will be kept strictly confidential using established processes. Data will be securely archived for 10 years after the completion of the study and then destroyed.

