#### Activity monitor (activPAL) data

Sedentary time, as measured by activPAL activity monitors, will be analysed as total sedentary minutes on an average day as well as the percentage of sedentary time during wake time. Data from the monitors will be automatically recorded and processed using the activPAL software (PAL Technologies). We will process data, remove sleep time and calculate, for each day, the total sedentary time; total sitting time accumulated in bouts ≥30 min, and bouts ≥60 min, number of sedentary bouts ≥30 min and bouts ≥60 min, total standing time, total stepping time and number of sit-to-stand transitions.

We will then calculate the key secondary outcome of mean daily sedentary time for the days when the monitor was worn. All other sedentary behaviour secondary outcomes will be calculated in the same way. The sedentary behaviour outcomes would ideally be based on 7 days of continuous wear of the monitor. The calculation of sleep time, definition of a valid wear day and number of valid wear days required for inclusion in the analysis will be informed by the results of earlier feasibility work.

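### The sealed activity monitor protects at most the raw recording; the derived sedentary-time endpoint can draw on an unblinded diary and is not free of bias

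*Protocol article*

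**What the plan says.** All references are to the protocol article.

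- **Endpoints:** "The key secondary endpoint is mean daily sedentary time (minutes) at 12 months post-registration using activity monitor (activPAL) data".
- **Randomisation and blinding:** the monitor "is sealed with no external indication of recording therefore it is not open to bias". The following paragraph adds that participants, the clinical staff delivering the intervention and "the statistical team analysing the outcome data, will not be blinded to treatment allocation". Local researchers who recruit and who administer the monitors are blinded.
- **Procedure:** participants keep a daily diary during the baseline wear period of 9 days. "This will capture if/when the monitor has been removed"; it also records "the time they went to bed and got up each day and whether they had episodes of sleep" during the day. Its stated role is to help with the analysis and with monitoring skin reactions.
- **Data management:** researchers check the monitor data, and where needed "additional details to aid interpretation will be sought from the recruiting site and/or participant diaries".
- **Activity monitor (activPAL) data:** the software records and processes the data automatically. Then: "We will process data, remove sleep time and calculate, for each day, the total sedentary time". Daily values are averaged over the days of wear. The sleep calculation and the valid-day rule are to be informed by earlier feasibility work.
- **Interventions:** one focus of Get Set Go is "Encouraging stroke survivors to monitor their own standing and moving".

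**The concern.** The article moves from a property of the device to a conclusion about bias. Sealing keeps anyone from reading or altering the posture signal during wear. It does not protect the later steps that turn the signal into waking sedentary minutes: deciding which lying or sitting time is sleep, which time is non-wear, and which days count.

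Those decisions can use self-report from people who know their arm. In the intervention arm, those people have been taught why standing and moving matter and encouraged to monitor their own. Participants also know that they are wearing a thigh monitor, so behaviour in the wear period may differ by arm whatever the diary says.

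Reducing sedentary behaviour is the key secondary objective. The article's strengths list presents the monitor as the objective measure, and the primary endpoint is self-reported. A reader planning the next trial would therefore lean on the activPAL contrast. If it carries a reporting difference while labelled free of bias, the pilot could misinform that decision.

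**Working it through.** The plan gives no effect size, SD or power for this endpoint, so there is no figure to reproduce. The check traces where bias can enter and bounds its size.

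**Step 1: where bias can enter.**

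| Stage | Protected by sealing? | Who influences it |
|---|---|---|
| Posture signal is recorded | Yes, against reading or altering | Device |
| Behaviour while wearing | No | Unblinded participant |
| Sleep and naps removed | No | Software, with the diary assisting; weight not stated |
| Non-wear and valid days | No | Software and researcher checks, with site or diary where needed |
| Comparison of arms | No | Unblinded statistical team |

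The article states that local data collectors are blinded. It does not state whether those who process the monitor files are.

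**Step 2: bound on the minutes outcome.** Daily sedentary time = sitting and lying minutes − minutes classed as sleep. Let d be the between-arm difference in reported sleep or naps (intervention minus control, min/day) with no difference in true behaviour. Let w be the share of that difference that reaches the classification: w = 0 if an algorithm alone sets sleep, w = 1 if the diary alone does.

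Shift in the contrast = −w × d.

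Every d and w below is an assumption. The table gives the absolute shift in min/day.

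| d (min/day) | w = 0 | w = 0.25 | w = 0.5 | w = 1 |
|---|---|---|---|---|
| 10 | 0 | 2.5 | 5 | 10 |
| 15 | 0 | 3.75 | 7.5 | 15 |
| 30 | 0 | 7.5 | 15 | 30 |
| 60 | 0 | 15 | 30 | 60 |

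The sign follows d. If intervention participants report more sleep (d > 0), the shift favours Get Set Go. If they under-report naps (d < 0), it goes against Get Set Go. An assumed d anywhere from −30 to +30 therefore gives a shift anywhere from +30 to −30 min/day at w = 1.

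If only one of the 7 ideal wear days is affected, the shift at w = 1 is d/7: 1.4, 2.1, 4.3 and 8.6 min/day for d = 10, 15, 30 and 60.

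**Step 3: the percentage outcome.** With S waking sedentary minutes and W wake minutes (both assumed), the shift at w = 1 is (S − d)/(W − d) − S/W. For d = 30:

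- S = 600, W = 900: 570/870 − 600/900 = 65.52% − 66.67% = −1.15 points.
- S = 700, W = 900: 670/870 − 700/900 = 77.01% − 77.78% = −0.77 points.
- S = 780, W = 960: 750/930 − 780/960 = 80.65% − 81.25% = −0.60 points.

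Misreported sleep leaves both numerator and denominator, so this outcome moves by about one percentage point or less.

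**Step 4: monitor removal.** Removal entries affect non-wear and the choice of valid days. They do not pass one for one into a mean over worn days, so Step 2 does not apply to them.

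**The case against.** The strongest reply is that the article never makes the diary the source of sleep time. The diary assists, it is consulted where needed, processing is automatic in the software, and the sleep rule is left to feasibility work. A largely algorithmic rule may already be the plan and may be set out in the full protocol or the statistical analysis plan. All of this stands, and the absence of a sleep or valid-day rule from the article is not counted against it.

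A reader might infer three stronger things, none of which the text supports:

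- **That sleep, naps and removal come from the diary, so bias enters minute for minute.** That is the upper bound only (w = 1), and only for the minutes outcome. The article says the diary records whether naps occurred; it does not say that their duration is logged.
- **That the bias favours Get Set Go by a known amount.** The documents give no size or sign.
- **That the processors are unblinded.** The article describes the unblinded statistical team as analysing outcomes, not as cleaning monitor files. It also refers elsewhere to blinded study researchers, and a query to a recruiting site may reach blinded staff. Masking of the processors is simply not stated.

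The diary is described in the baseline paragraph of Procedure, and the follow-up paragraph does not mention it. Its use at 12 months is a fair inference from Data management, but still an inference.

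The disputed sentence can also be read narrowly, as being about the device alone in a paragraph on data-collector bias. On that reading it is nearly true, but its wording is absolute and nothing separates the device from the endpoint derived from it. Reactivity during wear is common to unblinded behavioural trials, and masking the processors will not cure it; it can only be acknowledged. The exploratory status of the pilot lowers the stakes, but does not make the statement correct.

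**Conclusion.** The concern holds in limited form. The claimed freedom from bias applies at most to the raw recording. It does not carry over to mean daily sedentary time at 12 months, because sleep removal and wear decisions can draw on an unblinded diary, wear behaviour is unblinded, and masking of the processing is not stated.

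A reporting difference of d min/day would shift the contrast by between 0 and d, in either direction. For an assumed 30 min/day that is 0 to 30 min/day. The conclusion rests on two assumptions: that the diary is used at 12 months as at baseline, and that it has some weight in classifying sleep. If an algorithm alone sets sleep and wear, the diary route closes and only reactivity and unmasked handling remain. The point merits a change because the remedy is cheap and the endpoint serves the key secondary objective.

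**What to change.** 1. In Randomisation and blinding, limit the statement to the raw recording, and say that wear-period behaviour and the diary are unblinded.
2. State that sleep, wear and valid-day classification is done by processors masked to service and arm, and is locked before the data are merged with allocation. Masking to service matters because allocation is by service.
3. Add a sensitivity analysis of the key secondary endpoint in which daytime lying counts as sedentary whatever the diary says. It should state how daytime is delimited, because bed and get-up times would still matter if the diary sets them. It measures a slightly different quantity (true naps count as sedentary), so the useful comparison is whether the between-arm contrast changes.
4. Tabulate diary-reported naps and non-wear by arm, so that a reporting difference can be seen.

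The cost is masked identifiers for processing, one extra analysis run, one table and a wording change. No new data collection is needed if the diary is used at follow-up as at baseline. If the full protocol or analysis plan already provides for items 2 to 4, only item 1 remains.
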